##### Outcome 2: PrEP Retention at 6 Months Among FSWs Aged Between 18 and 24 Years

This will be measured as attendance within a window of −7 to +7 days of the scheduled 6-month refill visit. Outcome 2 will be expressed as the proportion of visits completed as scheduled, overall and by arm.

##### Outcome 3: Patronage for PrEP Services at Pharmacies

FSWs (overall) and FSWs (aged between 18 and 24 years) patronage for PrEP services at pharmacies, defined as the proportion of all PrEP refill pickups (1, 3, 6, and 12) in intervention suburbs occurring at pharmacies, overall and by pickup month.

#### Data Analysis for Aim 2

For retention outcomes at 1, 3, 6, 9, and 12 months, the KP program database will be used to compare the number and proportion of FSWs retained on PrEP as defined earlier by study arm. We will conduct an intent-to-treat analysis to estimate the intervention’s effect using a cluster-based permutation test applied to the individual-level binary outcome (retained on PrEP and not retained on PrEP) using the *cptest* function in the R cvcrand package (or a similar function). The permutation test will be conducted with the same covariates used during the constrained randomization process at the suburb level (expanded from the values of the cluster-level covariates, according to which cluster everyone belongs). This approach will be repeated for the other outcomes. To produce a measure of effect, a Generalized Estimation Equations model will also be constructed to generate a risk difference of PrEP retention among people initiating PrEP in intervention versus comparison suburbs and a 95% CI. In accordance with the CONSORT (Consolidated Standards of Reporting Trials) guidelines, unadjusted estimates will be reported, and the preregistered analysis plan at ClinicalTrials.gov will specify an adjusted model in the case of baseline imbalances. Overall, this analysis framework permits causal attribution.

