#### Overview of PrEP Services in the KP Program

The KP program requires verbal consent from SWs to dispense PrEP, which is freely available [5]. MoHCC implementation guidelines include free provider-delivered oral rapid HIV testing at initiation, along with provision of a 1-month supply of PrEP. The first refill provides a 2-month supply of PrEP, followed by 3-month supplies for subsequent refills (Figure 4). Free, provider-delivered oral rapid HIV testing will be offered every 3 months, and in accordance with the national PrEP guidelines, only individuals with confirmed HIV-negative results are offered future PrEP refills [47]. KP program data are collected on paper-based forms for all SWs who initiate PrEP routinely; these are used to generate a unique identification number for the SWs and an associated KP program file, which is essential for PrEP refill collection. People who do not return for refill visits are routinely followed up via phone calls, WhatsApp (Meta Platforms, Inc) reminders, and peer outreach. SWs are offered a US $5 transport reimbursement when collecting their PrEP refills routinely in the program.

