#### Procedure for Those Enrolled Through the PrEP-in-Pharmacy Intervention Arm

FSWs initiated on PrEP through the KP program’s mobile outreach clinics in the intervention suburbs will be informed about the intervention, namely, the opportunity to access PrEP refills either from selected pharmacies within the suburbs or through KP program clinics. In addition, the participants will also be informed that PrEP refills in the pharmacy warrant gift vouchers for the first 6 months of the trial, and no vouchers will be available for the remaining 6 months of the trial. Intervention arm participants initiating PrEP will be given a TOPAZ referral slip, which they can redeem at any participating pharmacy or KP program clinic. The same services provided at standard-of-care sites will be available through the pharmacy, namely, HIV testing, PrEP refills, adherence counseling, linkage to additional services, and the US $5 transport reimbursement in line with the KP program care. In addition, FSWs that opt to refill PrEP-in-pharmacies will be offered an incentive in the form of a gift voucher redeemable for products in the pharmacy wherein the refill was collected. The incentive will continue until month 6 and will escalate in value at each visit. Months 1, 3, and 6 will receive gift vouchers valued at US $5, US $6, and US $7, respectively. To measure retention on PrEP without incentive, participants will not receive a gift voucher in the last 2 refill visits of the intervention, that is, months 9 and 12; however, data will be collected. Implementing pharmacies will be given a TOPAZ study handbook with standard operating procedures for the intervention. In addition, the KP program will conduct weekly support visits to participating pharmacies.

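### Outcome 3 claims to count every refill pickup but leaves out month 9, the first of only two voucher-free pickups

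*Protocol article*

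**What the plan says.** Outcome 3 (protocol article, Outcomes) measures patronage for all FSWs and for those aged 18 to 24. It is "defined as the proportion of all PrEP refill pickups (1, 3, 6, and 12) in intervention suburbs occurring at pharmacies", and results are to be given overall and by pickup month.

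Three other places bear on which pickups exist:

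- **Overview of PrEP Services in the KP Program.** Initiation comes "along with provision of a 1-month supply of PrEP". After that, "The first refill provides a 2-month supply of PrEP, followed by 3-month supplies for subsequent refills".
- **Procedure for Those Enrolled Through the PrEP-in-Pharmacy Intervention Arm.** On vouchers: "Months 1, 3, and 6 will receive gift vouchers valued at US $5, US $6, and US $7, respectively". Then: "participants will not receive a gift voucher in the last 2 refill visits of the intervention, that is, months 9 and 12". The same sentence adds that data are still collected at these two visits.
- **Data Analysis for Aim 2.** The analysis opens "For retention outcomes at 1, 3, 6, 9, and 12 months".

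**The concern.** The definition contradicts itself. It claims to cover all pickups, then lists four of the five that the schedule produces.

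The missing one matters more than another month would. Vouchers are given only for pharmacy refills and only up to month 6. Months 9 and 12 are therefore the only pickups at which a woman chooses between pharmacy and clinic with no voucher attached to the pharmacy. The Discussion concedes that the trial cannot separate the voucher from the pharmacy, and looks to follow-up after month 6 for information on the intervention once vouchers have ended. An analyst who follows Outcome 3 literally would discard one of the two time points that can show what happens to pharmacy use then. The pooled figure would also lean further towards the months in which pharmacy collection was rewarded.

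**Working it through.** **Step 1: rebuild the pickup months.** The inputs are the supplies in the KP program overview: 1 month at initiation, 2 months at the first refill, 3 months at each later refill.

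- First refill: 0 + 1 = month 1
- Second: 1 + 2 = month 3
- Then 3 + 3 = month 6, 6 + 3 = month 9, 9 + 3 = month 12

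The schedule gives 1, 3, 6, 9 and 12. Outcome 3's list of 1, 3, 6 and 12 cannot be reproduced from it. The rebuilt list agrees with the voucher-free visits named in the intervention-arm procedures and with the retention months in Data Analysis for Aim 2.

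**Step 2: share of scheduled visits that carry a voucher** (months 1, 3 and 6).

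- As written: 3/4 = 75%
- With month 9: 3/5 = 60%

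**Step 3: share of pickups that carry a voucher.** Outcome 3 is a proportion of pickups, so attendance matters. The article gives no attendance by month, so the patterns below are assumptions. Two are set so that month 6 equals a figure in the sample-size section (50% or 14%) and attendance falls steadily; one has a steeper fall after month 6; one is flat.

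**Step 4: effect on pooled patronage.** Let s be the voucher share of counted pickups, pV the pharmacy share in voucher months and pN the pharmacy share in voucher-free months (taken as equal at months 9 and 12).

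- Pooled patronage = s × pV + (1 − s) × pN
- Shift from omitting month 9 = (s without 9 − s with 9) × (pV − pN)

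With pV = 80% and pN = 40%, both assumed:

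| Assumed attendance, months 1/3/6/9/12 (%) | s without 9 | s with 9 | Pooled without 9 | Pooled with 9 | Shift (points) |
|---|---|---|---|---|---|
| Equal at every visit | 75.0% | 60.0% | 70.0% | 64.0% | 6.0 |
| 80/65/50/40/30 | 195/225 = 86.7% | 195/265 = 73.6% | 74.7% | 69.4% | 5.2 |
| 80/65/50/25/15 | 195/210 = 92.9% | 195/235 = 83.0% | 77.1% | 73.2% | 4.0 |
| 50/30/14/10/7 | 94/101 = 93.1% | 94/111 = 84.7% | 77.2% | 73.9% | 3.4 |

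Shifts are computed before rounding.

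**Step 5: sensitivity to the assumed change in pharmacy use**, over the same four patterns.

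- 60% falling to 30%: 2.5 to 4.5 points
- 80% falling to 20%: 5.0 to 9.0 points
- 70% in every month: 0

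By the same formula the sign reverses if pharmacy use rises after vouchers stop.

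**The case against.** **It is probably a slip.** The word all governs the sentence, the next subsection lists five months, and month lists vary elsewhere: the Abstract and the Design section give retention at 3, 6, 9 and 12 months, without month 1. This is a fair account of how the error arose, and I do not read it as a deliberate choice. It remains a stated outcome definition that contradicts itself, and no section justifies it.

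**Reporting by month already covers it.** Results are to be given for pickups "in intervention suburbs occurring at pharmacies, overall and by pickup month", so month 12 stands on its own beside the voucher months, and a fall in pharmacy use could show there. This stands in part. Month 9 is not among the listed months, however, so by-month reporting does not recover it. Month 12 would be the only voucher-free point, and with continuing attrition probably the smaller of the two.

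**Voucher months dominate in any case.** This stands. With month 9 restored they are still 60% of scheduled visits and 74% to 85% of pickups under the falling-attendance patterns above. A reader might infer that the omission is what makes the pooled figure mainly a measure of rewarded use. The arithmetic does not support that.

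**Nothing decisive depends on it.** A reader might also infer that the go/no-go decision would be distorted. The progression criteria are a qualitative assessment from several sources and set no patronage threshold. Adoption in Table 2 is a separate count with no month list. The article does not show that either would exclude month 9.

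**Voluntary uptake is a different quantity.** The article does not present patronage as uptake without vouchers, because the intervention bundles the two. So it cannot be said that Outcome 3 overstates voluntary uptake as the article defines its own measure.

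**Conclusion.** The definition is wrong as written and should be corrected. That conclusion rests only on the article's own schedule and visit lists and needs no assumption. Its certain consequence is that one of only two voucher-free pickups is missing from both the overall and the by-month patronage results, and that voucher months rise from 3 of 5 to 3 of 4 scheduled visits.

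Any numerical effect on pooled patronage is conditional. It is zero if pharmacy use does not change when vouchers stop. It is about 3 to 6 points upward if use falls from 80% to 40%, an assumed fall that the article neither states nor supports. A claim of material bias, or of a compromised progression decision, would go beyond the document. Outcomes 1 and 2, the between-arm comparison and the power calculation are untouched.

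**What to change.** In Outcome 3, change (1, 3, 6, and 12) to (1, 3, 6, 9, and 12). Keep reporting overall and by pickup month, for all FSWs and for ages 18 to 24, so that months 9 and 12 can be read as patronage after vouchers stop. If month 9 was left out on purpose, the text should give the reason and drop the claim to cover all pickups.

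A pooled summary of voucher months (1, 3, 6) against voucher-free months (9, 12) is an optional addition, since by-month results already allow that comparison once month 9 is listed.

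The cost is one inserted number. The procedures state that month-9 data are collected ("that is, months 9 and 12; however, data will be collected"), and the article schedules the final analysis for February 2026, so the definition should be settled before that analysis is run.

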**Methods:**

Using a participatory process, the TOPAZ intervention will be collaboratively developed with pharmacy owners and SWs. TOPAZ comprises the provision of safe and convenient spaces for PrEP refill pickups bundled with a gift voucher incentive at pharmacies. Formative research comprising focus group discussions and in-depth interviews with SWs, pharmacists, and stakeholders will inform the development of the preliminary model (aim 1). A cluster-randomized pilot trial will evaluate the impact of the PrEP-in-pharmacy intervention, compared to standard clinic-based pickup in the key populations program, on PrEP retention at 3, 6, 9, and 12 months after initiation (aim 2). The outcome of the pilot trial will be a comparison of PrEP retention at 6 months after initiation between study arms. We will also compare PrEP retention among SWs aged between 18 and 24 years at 6 months and among participants remaining active in sex work at 6 months. We will use the Generalized Estimation Equations model to generate risk differences and 95% CIs for PrEP retention in intervention versus comparison arms. Analysis will follow an intent-to-treat approach. Finally, a mixed methods study will be conducted to understand the potential for scaling TOPAZ for SWs; insights from this study will inform the design of a future effectiveness trial (aim 3). Proctor’s implementation outcomes, namely, acceptability, adoption, appropriateness, feasibility, fidelity, and penetration of the pharmacy-based PrEP refill program, will be evaluated by triangulation of program data and qualitative interviews.

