#### Sample Size and Power Calculations

Data from our previous work indicate that current PrEP retention at 6 months post-PrEP initiation is 14% among FSWs in Harare. With 8 suburbs (4 per arm) and a target enrollment of 25 SWs per intervention suburb (totaling 100 participants in the intervention arm), and assuming an ICC of 0.12, the study will have ≥80% power to detect a 36% increase in PrEP retention—from 14% in the standard-of-care arm to 50% in the intervention arm. Note that this is a pilot trial and, consequently, is only powered to detect large effect sizes. If retention is lower than expected in the comparison group (eg, 10%), we will have at least 80% power to detect a ≥34% increase in PrEP retention. Likewise, if retention is higher than expected in the comparison group (eg, 30%), we will be adequately powered at 80% to detect a ≥38% increase in PrEP retention.

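### The risk difference and 95% CI come from a GEE on 8 clusters with no few-cluster safeguard named, and they are adjusted differently from the permutation test they accompany

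*Protocol article*

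**What the plan says.** The section Data Analysis for Aim 2 gives two tools separate jobs. The intention-to-treat comparison is a cluster-based permutation test on the individual binary outcome. It is specified down to the R function and uses the suburb-level covariates from the constrained randomisation. For the effect measure, "a Generalized Estimation Equations model will also be constructed to generate a risk difference of PrEP retention" between intervention and comparison suburbs, with a 95% CI. Unadjusted estimates are to be reported, and the registered analysis plan "will specify an adjusted model in the case of baseline imbalances".

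The abstract mentions only the second tool: "We will use the Generalized Estimation Equations model to generate risk differences and 95% CIs for PrEP retention". The permutation test does not appear there.

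The section Sample Size and Power Calculations sets the scale: "With 8 suburbs (4 per arm) and a target enrollment of 25 SWs per intervention suburb", "assuming an ICC of 0.12", and a contrast "from 14% in the standard-of-care arm to 50% in the intervention arm".

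The article does not state the working correlation, variance estimator, small-sample correction or reference distribution for the GEE.

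**The concern.** The usual GEE interval uses a sandwich variance and normal quantiles, and both rely on a large number of clusters. With 4 per arm, the sandwich is biased downward and 1.96 is too small a multiplier. The risk difference and its interval are the only effect measure planned for retention. They inform the design of a later effectiveness trial, and trial outcomes are among the inputs to two of the four progression indicators in Table 4. An interval that looks more precise than it is would mislead that planning.

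The second issue is coherence. The p-value is adjusted and randomisation-based, while the interval is model-based and unadjusted. A reader could be shown an interval that excludes 0 beside a permutation p-value above 0.05, and the article gives no rule for reading the pair. Making adjustment depend on observed imbalance adds an avoidable choice, because the suburb-level covariates are known before allocation.

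**Working it through.** **Inputs.** From the sample size section: 4 clusters per arm, 25 per intervention suburb, ICC 0.12, and 14% versus 50%, with alternatives of 10% versus 44% and 30% versus 68%. Assumed because the article does not give them: 25 per comparison suburb, two-sided 5% level, equal cluster sizes unless noted, beta-binomial clustering.

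**1. The plan's own power figure.** Design effect = 1 + 24 × 0.12 = 3.88, so the effective n per arm = 100/3.88 = 25.8. A two-proportion test with pooled null variance and normal quantiles gives power 0.810 (14% vs 50%), 0.804 (10% vs 44%) and 0.797 (30% vs 68%). The detectable differences are 35.5, 33.8 and 38.1 points, so the stated 36, 34 and 38 reproduce. With unpooled variance, power at 14% vs 50% is 0.852 with normal quantiles and about 0.71 with t on 6 df.

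**2. Closed form for an uncorrected interval.** With 4 equal clusters per arm, the sandwich variance of the risk difference has expectation (4 − 1)/4 = 0.75 of the true variance.
- Standard error ratio: √0.75 = 0.866, about 13% too small.
- Quantile ratio: 1.96/2.447 = 0.801, about 20% too small.
- Width relative to a corrected interval on t(6): 0.866 × 0.801 = 0.694, so 30.6% too narrow.
- Coverage: P(|t6| < 1.96 × 0.866) = P(|t6| < 1.697) = 85.9%, so the implied null error is 14.1%.

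**3. Simulation of the uncorrected interval.**

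| Setting | Coverage |
|---|---|
| Three design scenarios, ICC 0.12, cluster-level | 84.5-85.2% |
| 14% vs 50%, 1,500 identity-link exchangeable GEE fits | 85.7% |
| 14% vs 14%, ICC 0.12, cluster-level | 86.7% |
| 14% vs 14%, 1,500 GEE fits | 88.7% |
| Unequal clusters, assumed CV 0.4 | 82.8-84.4% |

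The null error at the 14% control rate is therefore 11.3% in the GEE fits (Monte Carlo standard error √(0.887 × 0.113/1500) = 0.8 points) and 13.3% in the cluster-level run.

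**4. Corrected intervals.** On t(6), a Kauermann-Carroll type correction gives about 93-96% coverage and a Mancl-DeRouen type about 96-97%.

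**5. Interval against test.** This step uses an unadjusted permutation test over all 70 allocations. At 14% vs 50%, ICC 0.12, it rejects in 48.3% of trials. The uncorrected interval excludes 0 while the test does not reject in about 38-39%; the reverse was not seen. With no effect, the figure is about 11%. After correction, disagreement at 14% vs 50% falls to about 22% (Kauermann-Carroll) or 14% (Mancl-DeRouen). So about 39 − 22 = 17 to 39 − 14 = 25 points are attributable to the missing correction. The remainder partly reflects coarse p-values: the smallest two-sided p is 2/70 = 0.029 and the next is 4/70 = 0.057.

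**The case against.** The strongest reply is that the article never says the GEE is uncorrected. It names the model only, and the variance estimator and degrees of freedom are details that an article may leave to an analysis plan, which is not shown here. That stands, and it makes the width and coverage figures conditional. A reader might infer from the normal-quantile power calculation that the GEE will be run the same way. The power section does not establish that, because it concerns sample size and not the interval.

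A second reply is that few-cluster inference is already handled. The permutation test does not rely on a large number of clusters, and the GEE is added only to supply an effect size. This also stands. A reader might conclude that the trial's formal false-positive rate is 11-14%. It is not: that rate applies only if the interval is read as a test. Nor does the abstract give the GEE primary status; it leaves out the permutation test.

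Third, the 38-39% disagreement should not be read as GEE error alone. Correction leaves 14-22%, and the size of the constrained allocation set is unknown.

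Fourth, unadjusted estimates are reported whatever the baseline looks like, so the imbalance trigger cannot replace them. That limits the adjustment point without removing it. The mismatch between an adjusted test and an unadjusted estimate is stated in the article and does not depend on any unseen plan.

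**Conclusion.** The point holds in conditional form. With 4 clusters per arm, unless a small-sample correction and a t reference are used, the 95% CI is about 31% too narrow with roughly 84-86% coverage, about 83-84% if cluster sizes vary (CV 0.4 assumed), and a null error of about 11-14%. At the design alternative it would exclude 0 without a permutation rejection in about 38-39% of trials, given 25 per comparison suburb, all 70 allocations and no covariates in the simulated test. The different adjustment of test and estimate, and the imbalance trigger, hold as written.

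Severity is moderate. The permutation test remains the formal test, the trial is a pilot, and progression is judged qualitatively, with no rule tied to this interval.

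**What to change.** In Data Analysis for Aim 2, state one of the following:
- The risk difference CI uses a small-sample-corrected sandwich variance (for example Kauermann-Carroll or Mancl-DeRouen) with t on 6 df, fewer if cluster-level covariates are included.
- The CI is obtained by inverting the permutation test, so that it agrees with the p-value. Check the size of the constrained set first: with fewer than 40 allocations the two-sided p cannot reach 0.05 (2/40 = 0.05), and a 95% interval by inversion would be uninformative.

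If the first option is chosen, say which result governs when the two disagree, because correction alone does not remove disagreement.

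Fix any adjusted model in advance on the constrained-randomisation covariates, and drop observed imbalance as the trigger. Name the permutation test in the abstract beside the GEE.

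The change costs a paragraph of text and a software option, or a short routine for the inversion. Data collection and conduct are unaffected. The price is wider intervals: relative to the uncorrected one, the Kauermann-Carroll interval on t(6) is 1/0.694 = 1.44 times as wide. Each cluster-level covariate also takes a degree of freedom from 6.

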#### Data Management

All data collected in this study will be managed and transmitted by a trained data manager. A study operation manual with data management and monitoring guidelines will be developed to ensure protection of participants’ confidentiality and minimal risks due to participation in the study.

